# Effectiveness of peer-led intervention in control of non-communicable diseases in rural areas of Khordha district: study protocol for a cluster randomized controlled trial

**DOI:** 10.1186/s13063-023-07824-w

**Published:** 2024-01-03

**Keywords:** Non-communicable diseases, Community health, Peer-lead intervention, Diabetes, Hypertension, Dyslipidaemia

## Abstract

**Background:**

The main contributors to death and disability from chronic illnesses in developing nations are elevated blood pressure (hypertension), blood sugar (diabetes mellitus), and blood cholesterol (dyslipidaemia). Even though there are affordable treatments, the treatment gap for these conditions is still significant. Few pilot studies from industrialized nations discuss the value of peer-led interventions for achieving community-level management of blood pressure and blood sugar. This study aims to evaluate the effectiveness of peer-led intervention compared to standard care in achieving control of selected non-communicable diseases (NCDs) in Indian context at 1 year of intervention among people of 30–60 years with hypertension and/or diabetes mellitus and/or dyslipidaemia.

**Methods:**

A cluster-randomized controlled trial will be conducted in villages of two rural blocks of the Khordha district of Odisha from August 2023 to December 2024. A total of 720 eligible participants (360 in the intervention group and 360 in the control group) will be recruited and randomized into two study arms. The participants in the intervention arm will receive a peer-led intervention model for 6 months in addition to standard care. The sessions will be based on the six domains of NCDs — self-care, follow-up care, medication, physical activity, diet, limiting substance use, mental health and co-morbidities. The mean reduction in blood pressure, HbA1C, and blood cholesterol in the intervention arm compared to the standard care arm will be the main outcome.

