### Objectives

The trial aims to evaluate the effectiveness of peer-led intervention compared to standard care in achieving control of selected NCDs at 1 year of intervention among people of 30–60 years with hypertension and/or diabetes mellitus and/or dyslipidaemia and to determine enablers and barriers to implementation of a peer-led intervention model among people of 30–60 years with hypertension and/or diabetes mellitus and/or dyslipidaemia.

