### Sample size

The sample size was calculated using nMaster 2.0 software (https://www.cmc-biostatistics.ac.in/nmaster/) with the formula for cluster study design:

$$n=\frac{{\left({z}_{\frac{\alpha }{2}}+{z}_{1-\beta}\right)}^2\left[{p}_1\left(1-{p}_1\right)+{p}_2\left(1-{p}_2\right)\right]\left[1+\left(m-1\rho \right)\right]}{{\left({p}_1-{p}_2\right)}^2}$$where *p*1 = proportion of outcome in the experimental group

*p*2 = proportion of outcome in the control group

*α* = level of significance

1-*β* = power

*ρ* = Intra-cluster correlation coefficient

*m* = size of the cluster

Considering the proportion of outcome in the control group as 50%, an alpha of 5%, power of 90%, effect size of 20%, design effect of 2.5 and loss to follow-up as 20%, the estimated sample size was 720 participants (40 clusters with 18 participants in each cluster) (Supplementary file 01).

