### Data collection and management

Data will be collected in epicollect5 and analysed using Statistical Package for Social Sciences (SPSS) Version 25 (IBM Corp.). Department of Community Medicine and Family Medicine, All India Institute of Medical Sciences, Bhubaneswar, had more than 10 years of experience for data collection and data management in various studies which includes national and international collaborative studies and various trials. The standard guidelines will be followed for data entry, coding, and storage. Categorical variables will be presented as percentages or proportions. Continuous variables will be presented as mean and standard deviation. Intention to treat analysis will be done to evaluate the effectiveness of peer-led intervention compared to standard care. The multivariate analysis will be performed to adjust for confounders. For missing variables, the replacement will be tried, if essential, based on the characteristics and quantiles of the variables. There won’t be any interim analysis and no formal trial-stopping rule, as this is a behavioural intervention study with no anticipated problems detrimental to the participant.

The effect of the peer-led intervention will be estimated by Difference in Difference (DID) analysis. A *p*-value of less than 0.05 will be considered statistically significant.

The outcome assessor is not aware of the link with intervention. At the end of one year (12 months) following *outcomes* will be assessed:Improved control status of Non-communicable diseases (hypertension and/or diabetes mellitus and/or dyslipidaemia) in the intervention arm compared to the standard care arm.Mean reduction of blood pressure in the intervention arm compared to the standard care arm.Mean reduction in HbA1C among diabetes mellitus patients in the intervention arm compared to the standard care arm.Mean reduction of blood cholesterol in the intervention arm compared to standard care.

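### The abstract's main outcome is three mean reductions, but the sample size and its 90% power are for a proportion, and no outcome is labelled primary

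*Protocol article*

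**What the plan says.** Abstract, Methods: the mean reduction in "blood pressure, HbA1C, and blood cholesterol in the intervention arm compared to the standard care arm will be the main outcome". That is three continuous outcomes, with no statement of whether all three or any one must succeed.

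Objectives (and the abstract's Background in similar terms): the aim concerns "achieving control of selected NCDs at 1 year of intervention", which is a matter of being controlled or not.

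Sample size: the formula is written in p1 and p2, p1 being the "proportion of outcome in the experimental group". The inputs begin "Considering the proportion of outcome in the control group as 50" per cent and continue with alpha 5%, power 90%, effect size 20%, design effect 2.5 and 20% loss to follow-up. The result is 720 participants, as 40 clusters of 18.

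Data collection and management: four outcomes are listed for 12 months. The first is "Improved control status of Non-communicable diseases (hypertension and/or diabetes mellitus and/or dyslipidaemia) in the intervention arm compared to the standard care arm". The other three are mean reductions in blood pressure, HbA1C and blood cholesterol. The HbA1C item reads "Mean reduction in HbA1C among diabetes mellitus patients in the intervention arm compared to the standard care arm". None of the four is called primary. One significance rule is given: a p-value "of less than 0.05 will be considered statistically significant".

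**The concern.** The primary outcome decides whether the trial succeeded, and the power statement and the 5% error rate refer to it. The article offers two candidates. The abstract leaves out the only binary outcome on the list, and the sample size section uses none of the outcomes that the abstract calls main.

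Two things are at stake. A reader of the abstract would attach 90% power to three mean reductions for which no power was calculated. And if control status and the means gave different answers, the article would not settle which of them is the trial's result.

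**Working it through.** **1. Which outcome does the stated power belong to?** Inputs from the Sample size section: control proportion 0.50; effect 20%, read as 20 percentage points, so 0.70 in the intervention arm; two-sided alpha 0.05; power 0.90; design effect 2.5; loss 20%.

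- Per arm, before clustering: (1.960 + 1.282)² × [0.7×0.3 + 0.5×0.5] / 0.2² = 10.507 × 0.46 / 0.04 = 120.8
- With the design effect: 120.8 × 2.5 = 302.1 per arm, 604 in total
- With loss added as a factor of 1.2: 604 × 1.2 = 725, against the stated 720

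The figure is reproduced as a two-proportion calculation. Reading 20% as a relative effect (50% versus 60%) gives about 3,090, so 20 points is the intended reading. (Dividing by 0.8 for loss would give 755; that is a separate matter.)

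**2. Can the power be carried over to the means?** This would need a target difference, an SD and an intra-cluster correlation for blood pressure, HbA1C and cholesterol. The article gives none of them, so neither a sample size nor a power can be computed from it. The following is illustrative, assuming the same design effect of 2.5, 20% loss and two-sided 0.05:

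- Effective number per arm: 360 × 0.8 / 2.5 = 115.2
- Standardised difference detectable with 90% power: 3.24 × √(2/115.2) = 0.43 SD
- Power for true differences of 0.2, 0.3 and 0.4 SD: 33%, 62% and 86%

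**3. HbA1C.** The baseline assessment measures HbA1C in everyone, and the 1-year assessment repeats the baseline. The outcome comparison is nevertheless limited to participants with diabetes, while eligibility requires only one of the three conditions. The number in that comparison is therefore below 720 and is not stated. The design effect of 2.5 with 18 per cluster implies a correlation of 1.5/17 = 0.088, which gives two bounds for each assumed share:

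| Assumed share with diabetes | Detectable difference, design effect rescaled to the smaller cluster | Detectable difference, design effect kept at 2.5 |
|---|---|---|
| 1/2 | 0.50 SD (design effect 1.71) | 0.60 SD |
| 1/4 | 0.62 SD (design effect 1.31) | 0.85 SD |

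On the HbA1C scale the answer depends heavily on the assumed SD. For a 0.5-point difference with 40% diabetic, n per arm = 288 × 0.4 = 115.2 and the design effect is 1 + (14.4×0.4 − 1)×0.088 = 1.42. Power = Φ(0.5/(SD×√(2×1.42/115.2)) − 1.96), which is about 89%, 57% and 36% for SDs of 1.0, 1.5 and 2.0. The difference, the SDs and the share are all assumptions.

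**4. Several outcomes, one threshold.** If every result were tested at 0.05 and any one counted as success, the chance of at least one false positive under independence would be 1 − 0.95³ = 14.3% for the abstract's three outcomes and 1 − 0.95⁴ = 18.5% for all four. These are illustrative ceilings. The outcomes are related, since control status draws on the same kinds of measurement as the means, and that relation lowers both figures.

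**The case against.** The best reply is that only one sentence departs from an otherwise consistent plan. The title, the objective, the sample size and the first listed outcome all point to control. That is largely right, and it is why the repair is easy. It does not remove the contradiction, because the departing sentence is the only place where any outcome is called main.

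A second reply is that multiplicity rules usually sit in an analysis plan, which may exist. This stands: the absence of a ranking or adjustment is not a finding here. Which outcome is primary, however, is something the article does state, and it states it inconsistently.

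A reader might also infer more than the documents support:

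- *That the trial is underpowered for the means.* This is not shown. If control reflects a normally distributed measure with a common SD, a shift from 50% to 70% equals about 0.52 SD. With 115.2 effective participants per arm, power for that shift in the mean is about 98%. Power for the means is unstated, not shown to be low.
- *That HbA1C is measured only in people with diabetes.* It is measured in all participants; only the comparison is restricted.
- *That the trial is sized on having all of one's conditions controlled.* The Sample size section says only that the outcome is a proportion. That it means disease control is itself inferred, from the objective and the only binary outcome listed.
- *That the 50% assumption is meaningless.* Control criteria for each condition are taken from national guidelines. Figures such as 12.5% (all of three controlled) or 87.5% (any of three) would need every participant to have all three conditions, each independently controlled in half. Eligibility requires only one, and for someone with one condition the two rules coincide. The combination rule for people with several conditions is not given in the article and may be in a fuller document.

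**Conclusion.** The concern holds as a contradiction within the article. The abstract's main outcome is three mean reductions; the objective and the first listed outcome are control; and the only sample size calculation is for a difference in proportions (725 recomputed against 720 stated). The stated 90% power cannot be claimed for the abstract's main outcome, and the article does not settle which of four results decides the trial.

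This conclusion rests on the text and on reading the 20% effect as percentage points. It would stand even if the sized proportion were something other than disease control, because no mean enters the calculation in any case. The detectable differences, HbA1C power and familywise error rates are illustrations under stated assumptions, and the conclusion does not depend on them. Because the primary outcome governs every confirmatory claim, the wording should be corrected before any outcome data are compared by arm.

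**What to change.** Name control status at 12 months as the single primary outcome, in the same words in the abstract and the outcome list. List the mean reductions in blood pressure, HbA1C and cholesterol as secondary. State in the Sample size section that the proportion used is the proportion controlled and that the 90% power applies to it alone.

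At the same time, state how control is scored for a participant with more than one condition, and confirm that the 50% control-group assumption fits that scoring. The choice of rule is the sponsor's; if 50% does not fit it, the sample size needs fresh justification.

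The cost is edits to the abstract, the sample size text and the outcome list, plus that one check. The mean changes lose main-outcome status. No extra measurements are needed, and no extra participants so long as the 50% is confirmed.

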**Discussion:**

The increasing burden of NCDs demands for newer strategies for management. Peer-led interventions have proven to be useful at the international level. Incorporating it in India will have remarkable results in controlling NCDs.

**Trial registration:**

Clinical Trial Registry of India (CTRI) CTRI/2023/02/050022. Registered on 23 February 2023.

**Supplementary Information:**

The online version contains supplementary material available at 10.1186/s13063-023-07824-w.

## Background and rationale

Non-communicable diseases (NCD) account for 71% of worldwide deaths [1]. Evidence suggests that 85% of premature deaths between 30 and 69 years are estimated to occur in low- and middle-income countries [1]. The cardiovascular mortality rate in India is the highest globally, twice that of the USA and three to five times more than European countries [2]. Currently, India is considered the capital of non-communicable diseases because of its burden. In India, 62% of all deaths and 55% of all disability-adjusted life years (DALYs) can be attributed to NCDs [3].

Hypertension, diabetes mellitus and dyslipidaemia are the most common non-communicable diseases [1]. An estimated 46% of adults with hypertension are unaware that they have the condition [4]. However, only one in five adults (21%) with hypertension have it under control [4]. Similarly, only 23.4% of patients with type 2 diabetes mellitus in India have reasonable glycemic control [5]. ICMR-INDIA study estimated that 79% of men and women had abnormalities in at least one of the lipid parameters [6]. Hypertension, diabetes mellitus and dyslipidaemia share common risk factors. Experiences and theories from India further suggest that a community-based approach, including individual empowerment, community empowerment, and raising critical consciousness, plays a pivotal role in controlling and preventing NCDs [7]. Adherence to pharmacological interventions and lifestyle modifications requires behaviour change that is challenging to achieve at the individual level or clinical care. However, interpersonal influences (such as peers) and environment are vital in changing behaviour [8]. Therefore, peer-led intervention with a community-based approach emerges as a relevant tool for controlling NCDs. Peer-led interventions are not explored in the Indian context for NCDs however found to be successful for alcoholic dependence [9] and weight reduction [10]. Studies from developed countries have shown that peer-led interventions effectively develop NCD knowledge, improve skills, and build confidence in managing their conditions [11]. These studies are primarily focused on glycemic control and improvement of knowledge, and two studies are on reducing blood pressure by peer-led intervention [12–16]. The hour needs to develop and validate integrated, comprehensive peer-led intervention addressing major NCDs that is feasible and culturally adaptable. In this study, along with the development and validation of the peer-led intervention model, we are trying to test the effectiveness peer-led intervention model through cluster-randomized control.

Raised blood pressure (hypertension), blood sugar (diabetes mellitus), and blood cholesterol (dyslipidaemia) are the leading contributing causes of mortality and disability from chronic diseases in developing countries. The treatment gap for hypertension, diabetes and dyslipidaemia remains high even though cost-effective treatment is available. Similarly, compliance with lifestyle modifications (physical activity, dietary recommendations and substance use) remains a challenge at the individual level. To control chronic disease, adherence to lifestyle modifications and pharmacotherapy plays a critical role in changing behaviours. Social norms theory states that the efforts that target interpersonal influences (such as peers) and environment yield better results than those targeted toward the individual in adopting new behaviours or changes in behaviours [8]. Peer supporters generally offer three types of support: emotional, appraisal and informational. Emotional support enhances morale through caring, empathy, encouragement and reassurance. Appraisal support includes:Encouraging persistence and optimism for resolving problems.Affirming a peer’s feelings and behaviours.Reassuring that problems can be solved.

Informational support involves providing advice, suggestions, alternative ideas, feedback, and factual information relevant to the peer’s issue [17]. Therefore, peer-led interventions become relevant to improve self-care, enhance community engagement, support the treatment of NCDs and protect vulnerable populations from a complication of NCDs.

Peer-led interventions to control NCDs are not explored in the Indian context. Few pilot studies are there from developed countries and their importance for controlling blood pressure or blood sugar at the community level. Our study aims to evaluate a peer-led intervention model that is flexible, culturally adaptable and helps to control major NCDs through community engagement improving adherence to lifestyle modifications and pharmacotherapy.

### Objectives

The trial aims to evaluate the effectiveness of peer-led intervention compared to standard care in achieving control of selected NCDs at 1 year of intervention among people of 30–60 years with hypertension and/or diabetes mellitus and/or dyslipidaemia and to determine enablers and barriers to implementation of a peer-led intervention model among people of 30–60 years with hypertension and/or diabetes mellitus and/or dyslipidaemia.

### Trial design

This is a cluster randomized controlled parallel-group trial with a superiority framework. Village is a cluster in the study. Villages will be randomized to two study arms with a 1:1 allocation ratio. The participants in the intervention arm will receive a peer-led intervention model for six months in addition to standard care.

## Methods: participants, intervention, outcome

### Study setting

The trial will be conducted in Mendhasal and Tangi block of Khurdha district of Odisha, India.

### Eligibility criteria

The case definitions and control criteria for hypertension, diabetes mellitus, and dyslipidaemia will be taken from standard national guidelines [18, 19]. Persons in the 30–60 years group with hypertension and/or diabetes mellitus and/or Dyslipidaemia will be recruited in the study based on the following criteria:

#### Inclusion criteria

Cluster level: villages under rural field practice areas of All India Institute of Medical Sciences, Bhubaneswar.

Individual level: persons with hypertension and/or diabetes mellitus and/or dyslipidaemia aged 30–60 years and residing in the same village for the last six months.

#### Exclusion criteria

Cluster level: Villages within 5 km of the community health centre (CHC).

Individual level:Patients who cannot communicate (hearing loss, diagnosed psychosis, etc.)Patient with diagnosed complications such as myocardial infarction, stroke, heart failure and advanced liver disease.Debilitated patients.

### Sample size

The sample size was calculated using nMaster 2.0 software (https://www.cmc-biostatistics.ac.in/nmaster/) with the formula for cluster study design:

$$n=\frac{{\left({z}_{\frac{\alpha }{2}}+{z}_{1-\beta}\right)}^2\left[{p}_1\left(1-{p}_1\right)+{p}_2\left(1-{p}_2\right)\right]\left[1+\left(m-1\rho \right)\right]}{{\left({p}_1-{p}_2\right)}^2}$$where *p*1 = proportion of outcome in the experimental group

*p*2 = proportion of outcome in the control group

*α* = level of significance

1-*β* = power

*ρ* = Intra-cluster correlation coefficient

*m* = size of the cluster

Considering the proportion of outcome in the control group as 50%, an alpha of 5%, power of 90%, effect size of 20%, design effect of 2.5 and loss to follow-up as 20%, the estimated sample size was 720 participants (40 clusters with 18 participants in each cluster) (Supplementary file 01).

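### The stated sample size of 720 does not follow from its own inputs, which give 756 at 20% loss; whether power falls below 90% depends on the cluster size to which the design effect of 2.5 belongs

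*Protocol article*

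**What the plan says.** The Sample size section of the protocol article gives a formula for comparing two proportions in a cluster design, with the normal quantile taken at half of alpha, the unpooled variance and a multiplier for clustering. The inputs follow in one sentence. It opens "Considering the proportion of outcome in the control group as 50"% and, after an alpha of 5%, continues "power of 90%, effect size of 20%, design effect of 2.5 and loss to follow-up as 20"%. The result is that "the estimated sample size was 720 participants (40 clusters with 18 participants in each cluster").

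Under Trial design, "Villages will be randomized to two study arms with a 1:1 allocation ratio". The Abstract gives 360 participants per arm, and Sequence generation gives 20 villages per arm. The section refers to Supplementary file 01, which is not among the documents at hand. It does not say how the loss was applied, and it names the intra-cluster correlation in the formula without giving it a value.

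**The concern.** The article puts formula, inputs and result side by side, so a reader can check one against the other, and they do not agree. A number of evaluable participants is turned into a recruitment target by dividing by the fraction expected to remain. Here that gives more than 720. Seen from the other end, 720 less 20% leaves fewer participants than the formula requires at the stated design effect.

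At stake is whether the 90% power claim can be relied on, and whether the sample-size justification can be reproduced by anyone who later judges the trial's result.

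**Working it through.** **Inputs, all from the Sample size section unless noted**
- Control proportion p2 = 0.50.
- "effect size of 20"%, read as 20 percentage points, so p1 = 0.70 (0.30 gives the same result). A relative 20% (60% against 50%) would need more than 2,500 participants before any allowance for loss, so it cannot be the source of 720.
- Two-sided alpha 0.05 (z = 1.960) and power 0.90 (z = 1.2816).
- "design effect of 2.5", entered directly as the clustering multiplier.
- "loss to follow-up as 20"%.
- "40 clusters with 18 participants in each cluster", with 1:1 allocation (Trial design).

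**Evaluable participants required**

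n per arm = (1.960 + 1.2816)² × (0.70 × 0.30 + 0.50 × 0.50) / 0.20² = 10.507 × 0.46 / 0.04 = 120.8

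With clustering: 120.8 × 2.5 = 302.1 per arm, or 604 in total.

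**Trying to reproduce 720**

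| Allowance for 20% loss | Total |
|---|---|
| 604.2 × 1.2 | 725.0 |
| 120 × 2.5 × 1.2 per arm, two arms (120.8 cut to 120) | 720 |
| 604.2 / 0.8 | 755.2, so 756 |

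Only multiplication by about 1.2 comes near the stated figure. Other variants at two-sided 5% and 90% power do not reach it. Pooled variance gives 744 (× 1.2) or 775 (/ 0.8). A continuity correction gives 804 or 838.

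756 is 378 per arm, or 21 villages of 18 per arm. 720 is 36 fewer, or 36/756 = 4.8% below it.

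**What 720 leaves after loss**

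720 × 0.8 = 576, or 288 per arm and 14.4 per village, against 604 required: a gap of 28.

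**Power, case A: design effect still 2.5 after loss**

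Effective size per arm = 288 / 2.5 = 115.2

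Power = Φ(0.20 / √(0.46 / 115.2) − 1.960) = Φ(3.165 − 1.960) = 88.6%

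With the pooled variance it is 87.8%. In this case the loss that still leaves 90% power is 1 − 604.2/720 = 16.1%.

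**Power, case B: 2.5 was set at 18 per village**

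The implied intra-cluster correlation is (2.5 − 1)/(18 − 1) = 0.088. This is an assumption, as the article gives no value.

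Design effect at 14.4 per village = 1 + 13.4 × 0.0882 = 2.18

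Effective size per arm = 288 / 2.18 = 132.0

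Power = Φ(0.20 / √(0.46 / 132.0) − 1.960) = Φ(3.388 − 1.960) = 92.3%

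With the pooled variance it is 91.7%, and with a t reference on 38 degrees of freedom it is 91.0%. In this case about 34% could be lost before power by the protocol's formula reached 90%: 11.88 would remain per village, with design effect 1.96 and 20 × 11.88 / 1.96 = 121.2 effective per arm, against 120.8 needed.

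**The case against.** The strongest reply is that the formula defines its cluster-size term as the size of the cluster, and 18 is the only cluster size in the article. The natural reading is then case B: the design effect shrinks as villages lose participants, and 720 is more than enough. This stands. A reader might infer from 576 against 604 that the trial is underpowered, that 720 can absorb only 16% loss, or that one of the four stated figures must be abandoned. The documents support none of these unconditionally. Each holds the design effect at 2.5 while the villages shrink, and the article does not say that this was intended.

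The size is modest even on the unfavourable reading: 1.4 percentage points below target by the protocol's own formula. A t reference on 38 degrees of freedom lowers case A to 87.0%, but that should not be quoted as the effect of the loss allowance. The protocol's formula uses no t reference, and by the same method 756 participants in 42 villages would reach only 88.6%.

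The multiplication by 1.2 is an inference. The text does not state it, it gives 725 and not 720, and the supplement may set out the steps. It can be called consistent with the figure and no more.

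Two side issues carry little weight. The printed clustering factor, taken literally, is 1 + m − ρ, about 19 at m = 18. That is a misplaced bracket with no numerical effect, because 2.5 is entered directly. The missing value for the intra-cluster correlation is a detail that an article may leave to its supplement, and it is not a fault in itself.

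What the reply does not remove is the mismatch. By the formula and inputs as printed, with the design effect given as a single number, the answer is 756 and the article says 720.

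**Conclusion.** The point holds as an inconsistency in the sample-size statement. The stated inputs give 604 evaluable and 756 recruited; the stated 720 leaves 576. It does not establish that the trial is underpowered. Power after 20% loss is about 88.6% if the design effect is 2.5 after loss, and about 91 to 92% if 2.5 belongs to 18 per village. The article does not say which applies.

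This rests on reading the 20% effect as percentage points, on a two-sided test as the formula shows, on the usual form 1 + (m − 1)ρ for the clustering factor, and, in case B, on losses spread evenly over the villages. The mismatch is worth correcting because it sits in the core design statement, but its likely effect on the trial is small.

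**What to change.** Keep 40 villages of 18 and restate the sentence so that the result follows from the inputs, in one of two ways:

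1. If 2.5 is meant as the design effect among those retained: *720 participants give about 88 to 89% power at a design effect of 2.5 with 20% loss to follow-up* (equivalently, 90% power with about 16% loss).
2. If 2.5 was set at 18 per village: state the intra-cluster correlation (0.088 if that is the value behind it), the 14.4 retained per village, the design effect of about 2.18 there, and the power of about 92% by the protocol's formula (91% with a t reference on 38 degrees of freedom).

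The authors can choose between them from their own working. In the same edit, move the bracket so that the factor reads 1 + (m − 1)ρ.

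The cost is wording only. No villages or participants are added and no analysis changes. The price is either a slightly lower stated power or an explicit assumption about the intra-cluster correlation.
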